### Short Message Service–Based Adherence Support

SMS-based adherence support is provided as part of the combination package with PrEP, in addition to standard adherence counseling. Adherence has been a significant challenge to the efficacy of PrEP and may be an important challenge for PrEP effectiveness. A 2014 systematic review and meta-analysis demonstrated that text-messaging interventions effectively supported adherence to PrEP more than control groups and were also associated with improved viral load and/or CD4 counts for individuals on antiretroviral therapy (ART) [24]. Text message reminders that were sent less frequently than daily tended to have greater effects [24]. Weekly SMS adherence prompts are therefore offered to participants choosing PrEP. SMS adherence prompts are dispatched through FrontlineSMS, with additional management by the research team. For participants agreeing to weekly prompts, participants’ FrontlineSMS profiles are configured for adherence messaging at the visit in which they initiate PrEP. The FrontlineSMS participant profile can be updated for any changes in PrEP use or for changes in timing of prompts, mobile device numbers, or carrier.

### Study Population

Eligible young MSM and TGW participants must meet the following key criteria: assigned male sex at birth; aged 18 to 26 years; HIV-negative at baseline testing; self-report that they have sold or exchanged sex to cis-gender men for money, drugs, or other goods in the past 12 months; self-report living in greater Bangkok metropolitan area or Pattaya; are Thai citizens; and are willing and able to complete study instruments. Participants do not have to self-identify as MSM or TGW, although such terms will be used in recruitment scripts to attempt to recruit participants from these populations.

Additional eligibility criteria for PrEP includes the following: HIV-negative at the visit (if acute HIV symptoms, can start PrEP at a subsequent return visit if the nucleic acid amplification test [NAAT] is negative); estimated creatinine clearance (eCrCl)≥60 mL/min; no major known allergy to tenofovir and/or FTC or the combination of the two; and able and willing to follow the PrEP prescribing guidelines.

### Recruitment and Consent

Convenience sampling methods are used, recruiting participants from a variety of venues including bars, clubs, saunas, brothels, karaoke parlors, cabarets, street-based locations, and other venues frequented by young MSM and TGW. These currently include 68 venues mapped by SWING in their 2015 census of venues in Bangkok. Outreach and recruitment are conducted by staff who have been trained in confidentiality and study procedures.

Recruitment also occurs online, using materials such as videos and fliers developed in collaboration with the community and produced by APCOM [25]. Staff are trained on how to avoid coercing individuals to participate in the study. Recruitment materials are posted on dating apps, Facebook, and other frequently used online venues. These recruitment materials also serve to raise awareness about and increase demand for PrEP. In addition, the study website, study clinic websites, and Facebook pages are used to provide community-wide access to information about services and the goals of the study [26]. All interested individuals are invited to contact the study staff for preliminary screening and to learn more about the study. Figure 2 displays an example study flier for MSM and TGW.

Study participants are invited to refer peers to the study. Participants are provided study information cards that they can distribute to potentially eligible peers who are MSM or TGW who are newly engaged in sex work or who have recently exchanged sex. Referred peers may be enrolled into the study upon meeting inclusion criteria. Participants who successfully recruit peers are compensated per similar standard practices implemented in the LINKAGES program in Thailand to support peer referral to HIV testing and care [27]. Study participants will be reminded to maintain confidentiality before referring peers and distributing information cards.

Candidate participants are not screened in person during recruitment events or peer or community referrals. Interested individuals are provided study information cards with a phone number, email address, and link to a website with more information about the study eligibility criteria, purpose, available clinics, and clinic hours. Interested individuals may indicate whether they would prefer to call the study offices to schedule an appointment at their own convenience or to provide their phone number and be contacted by study staff. During the initial phone call with study staff, candidate participants are informed of the study purpose and eligibility criteria and determine whether or not they would like to proceed with study recruitment. Aggregate data are collected from these phone calls on the number of individuals contacted or who contacted the study, those that were scheduled, and reasons not scheduled.

Consent is obtained from recruited young MSM and TGW, and they are screened for eligibility in private at one of the study sites. Those who are eligible are enrolled in the study. The screening visit includes an assessment of demographic criteria and rapid HIV testing. Participants identified with HIV infection complete their screening visit, including facilitated referral to care but do not attend any study follow-up visits. Participants who are determined to be living with HIV at their screening visit do not count toward the target sample size. At baseline, participants are also screened for hepatitis B and may initiate the vaccine series during follow-up, if susceptible.

Participants who are identified as being HIV-uninfected by rapid HIV testing are prospectively enrolled into the study. Enrolled participants are offered a combination prevention intervention package, with the option to initiate daily PrEP. Prospectively enrolled participants have an initial follow-up period of 12 months; participants who complete their 12-month follow-up period, regardless of PrEP initiation status, are offered the option of further extending their follow-up for another 12 months if the study timeline permits.

**Figure 2 figure2:**
[figure not shown]
Promotional flier for the Combination Prevention Effectiveness Study for young men who have sex with men and transgender women, Thailand.

### Study Visits

Participants, regardless of PrEP initiation, have standard follow-up study visits every 3 months (quarterly) that include HIV testing and counseling, condom and lubricant distribution, and surveys using computer-assisted self-interview (CASI) or with audio-assisted CASI (ACASI) technology. Participants are screened for syphilis, rectal gonorrhea, and chlamydia at their baseline study visit and every 6 months (semiannually) thereafter. Table 1 describes data collection activities that take place quarterly or semiannually, regardless of PrEP use. Through these visits and biological and survey outcomes, the study staff are able to assess the acceptability, uptake, adherence, and effectiveness of the combination intervention package for young MSM and TGW.

At any time during the study period from baseline to the 9-month visit, participants can be screened for PrEP eligibility with point of care creatinine testing. If eligible, they can initiate PrEP at that visit. Ineligible participants, or participants who do not express an interest in initiating PrEP during the initial 9-month study period may continue study participation as non-PrEP participants. Non-PrEP participants complete quarterly study visits and receive all standard procedures, including the CASI, HIV testing, hepatitis and STI testing, and DBS collection.

All participants initiating PrEP complete a PrEP monitoring visit 1 month after PrEP initiation to assess for acute HIV symptoms and provide adherence support. Participants on PrEP are then asked to complete monthly visits for medication pickup. Medication pickups can be combined with quarterly study visits during months in which they are due.

Participants can initiate, discontinue, and restart PrEP at any point during the study period. Changes to PrEP use can be communicated during any study visit, via weekly SMS surveys, or can be communicated to study staff outside of study visits. Reasons for discontinuing PrEP are recorded. Participants who restart PrEP after more than 2 weeks cessation must be rescreened. Study investigators consider someone stopped on PrEP if the participant’s weekly SMS adherence measures indicate that he/she had 2 consecutive weeks with 0 to 3 doses taken, or if the participant has >16 pills remaining from the month during a medication pickup. PrEP rescreening includes HIV testing and an assessment of willingness to commit to PrEP adherence. Participants who stop PrEP may continue in the study and continue with their remaining quarterly study visits. Participants who permanently stop PrEP or who do not want to immediately restart PrEP are instructed to return all Truvada as soon as possible.

Participants who seroconvert during the study period complete a close-out survey, receive facilitated referral to care with assistance by the case manager or site coordinator at each site, are discontinued from the study and do not attend subsequent study visits.

**Table 1 table1:** Description of quarterly and semiannual study visits for the Combination Prevention Effectiveness Study for cisgender men who have sex with men and transgender women, Thailand.

Study visit	Description
Quarterly study visits (every 3 months)	Confirm participant contact and locator information Administer CASI^a^ behavioral questionnaire Assess participant experience and impacts of study participation (including adverse events and social harms) Screen for signs and symptoms of acute HIV infection Provide HIV testing (including pooled NAAT^b^ testing if the participant has symptoms of acute HIV infection) Collect DBS^c^ for storage Distribute condom and lubricant
Semiannual study visits (every 6 months)	All procedures conducted at quarterly study visits Syphilis testing Rectal swab collection for rectal gonorrhea and chlamydia testing Serum creatinine measurement and estimated creatinine clearance calculation (for participants on PrEP^d^)

^a^CASI: computer-assisted self-interview.

^b^NAAT: nucleic acid amplification test.

^c^DBS: dried blood spots.

^d^PrEP: pre-exposure prophylaxis.

### Behavioral Survey

Sociodemographic and behavioral data are collected from all participants at baseline and at each follow-up visit using a standard survey. The survey is administered using CASI or ACASI depending on participant preference. Use of CASI on a standard personal computer or tablet occurs in a structurally secluded and quiet area at the study clinic to ensure confidentiality and to encourage candid disclosure of risk behavior. Trained staff are available to answer questions pertaining to the survey questionnaire.

Survey questionnaires span the following domains and are administered over the course of the study: sociodemographic; knowledge, awareness, and use history of PrEP, postexposure prophylaxis, or ART; health care utilization; engagement in the lesbian, gay, bisexual, and transgender (LGBT) communities; postrecruitment questions; sexual risk behavior; stigma; substance abuse; and mental health. Additional information on the focus of each domain is provided in Table 2.

**Table 2 table2:** Sociobehavioral survey domains, descriptions, and measures for the Combination Prevention Effectiveness study for young cisgender men who have sex with men and transgender women, Thailand.

Domain	Description
Sociodemographic	Information collected in this domain includes, but is not limited to, age, education, income, mobility, and insurance status.
PEP^a^/PrEP^b^	Information collected in this domain focuses on initial knowledge, awareness, acceptability of and attitudes about PEP/PrEP, and history of use (including recreational use and source of PEP/PrEP).
Sexual risk behavior	Information collected within this domain includes information on number and types of partners (sex work client, nonpaying casual, and stable relationship), frequency and types of sexual acts, condom use during intercourse, and location of the sexual experiences. This includes details on sex work (initiating and stopping), average number of clients per night and week, average number of nights worked per week, and regular/noncommercial sexual partners.
Health care utilization	Information collected in this domain includes information on health care utilization and services to assess engagement at baseline. Information in this domain is also collected at the final visit to assess any supplemental services that have been accessed outside the study.
Engagement in the MSM^c^, TGW^d^, and sex work communities	Information collected in this domain includes information on knowledge of and engagement within community forums, PrEP-related contact with outreach workers, social support, connection and collective efficacy within the LGBT^e^ community and in the sex worker community, and perceived support for PrEP and related topics within these communities. Receipt of condoms and contact with outreach workers will also be assessed. This domain allows the team to evaluate the effectiveness of the community mobilization intervention component.
Stigma	Information collected in this domain is focused on self-stigma (internalized homonegativity). This survey domain is adapted from Herek et al [28].
Substance abuse	Information collected in this section includes information on any substances used (amphetamine type substances, alcohol, etc) particularly around sexual experiences and frequency of substance use.
Mental health	The information collected in this section focuses on brief depression, posttraumatic stress disorder, and anxiety screeners using the Substance Abuse/Mental Illness Symptoms Screener [29,30].

^a^PEP: postexposure prophylaxis.

^b^PrEP: pre-exposure prophylaxis.

^c^MSM: men who have sex with men.

^d^TGW: transgender women.

^e^LGBT: lesbian, gay, bisexual, and transgender.

### Weekly Short Message Service Surveys

An open-source software, FrontlineSMS, is used to survey participants via text messages (SMS). FrontlineSMS is able to send and receive messages, respond to messages, and trigger other events. FrontlineSMS is programmed with the cell phone number of the study participant after study enrollment, informed consent, and selected preventive option. Through FrontlineSMS, weekly, brief behavioral surveys are sent to participants to obtain information on exchange sex and condom use in the last week. For participants currently using PrEP, additional measures are used to collect information on when they last took PrEP and the number of doses of PrEP taken within the last 7 days. For those reporting less than 4 doses, additional questions inquire about intention to continue taking PrEP, and, if applicable, reason for discontinuing PrEP use. To ensure participant privacy, SMS surveys are only unlocked by a unique code assigned to each participant upon registration. Participants who are unable to immediately complete an SMS survey because of privacy concerns may opt to postpone their response within an allowable timeframe. Participants will receive cash compensation (30 THB, equivalent to approximately US $1) for responding to reminders and to reimburse cellular data costs.

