### Setting and Context

In Thailand, sex work is not legal, but there are open and clear channels for community engagement. There is an openness and accessibility to those practicing sex work, and a substantial sex tourism industry, estimated to be US $6.4 billion a year as of 2015 [20,21]. The COPE study is centrally focused on PrEP implementation and effectiveness for young MSM and TGW who are engaged in sex work or otherwise exchanging sex for money, substances, or other items of value (here forward broadly referred to as *exchange*) in Bangkok and Pattaya, and who are at highest risk for HIV acquisition. As the early period of exchanging sex is a very high-risk period for HIV acquisition, this study aims to address risk for young MSM and TGW who are newly entering sex work or exchanging sex.

The study was initially proposed for MSM engaged in the sex work/exchange but was expanded to include TGW in response to community requests. Sexual and gender identities are not distinct in Thailand as they are in Western cultures, and although we use terms MSM and TGW that are accepted in the scientific literature, these broadly include approximately 15 unique identities that encompass both sexual and gender identities and expression [20,22]. MSM and TGW who exchange sex have overlapping communities and venues and are often served by the same organizations; thus, it was determined to be appropriate and equitable to extend this intervention to both groups.

This research effort is highly integrated with Thailand national policy development around the integration of PrEP into national HIV programming for MSM and TGW. The government provides free PrEP to key populations through community-based programs but has called for the development of appropriate implementation models for PrEP and cost-effectiveness analyses to support policy decisions on government-supported PrEP distribution for key populations. As a result, several community-based clinics have been established and trained to provide PrEP, including clinics operated by the Rainbow Sky Association of Thailand (RSAT) and Service Workers In Group (SWING) Foundation.

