The COPE study is supported by a joint collaboration between the Thai Ministry of Public Health (MOPH) and the United States Centers for Disease Control and Prevention (US CDC; known as the Thai-US Collaboration [TUC]) and in partnership with Mahidol University, Emory University, Johns Hopkins University School of Public Health, CBOs, SWING, RSAT, and the Asia Pacific Coalition on Male Sexual Health (APCOM). Primary implementation is at Silom Community Clinic (SCC) Clinical Research Site, operated by TUC. All recruitment and study implementation activities are done through SCC, SWING, and RSAT sites in Bangkok and SWING in Pattaya. Each study site has a site coordinator who provides oversight on study activities and communicates regularly to the multisite coordinator and study coordinator. Research teams also provide a physician-in-charge who is responsible for all clinical activities and care provided at each study site.

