### Daily Oral Pre-Exposure Prophylaxis

Daily oral PrEP with adherence support is offered to all participants (open label). Tenofovir disoproxil fumarate (TDF) and FTC (locally known as Teno-EM) is approved for PrEP in Thailand. The PrEP drug for the COPE study is Truvada, which contains identical chemical components as Teno-EM. The tablet includes 200 mg of FTC and 300 mg of TDF. Truvada is approved for treatment in Thailand (registration number: 2C 28/2551[NC]) and is manufactured and donated by Gilead Sciences for the COPE study. Truvada is a once daily oral tablet taken with or without food.

Participants who take PrEP are counseled on the mild side effects that are expected with Truvada including nausea, headache, abdominal pain, rash, and flatulence. They are also counseled to avoid medications with potential drug interactions as outlined in the 2014 Clinical Practice Guideline, CDC [23]. These include acyclovir, valacyclovir, cidofovir, ganciclovir, valganciclovir, aminoglycosides, high-dose or multiple nonsteroidal anti-inflammatory drugs, or other drugs that reduce renal function.

Participants on PrEP have monthly medication pickups for the entire duration they are using PrEP. At each monthly medication pickup, participants return to their selected clinic for the following procedures: unused medication drop-off, tablet count adherence, dispensing of one 30-tablet bottle of Truvada; collection of dried blood spots (DBS) for storage; assessment of signs and symptoms of acute HIV infection; assessment of side effects associated with PrEP use; and adherence assessment and counseling, informed by weekly SMS survey responses.

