### Data Analysis

Each week of study participation at risk for HIV for each participant falls into 1 of 4 mutually exclusive categories of person-time: (1) on PrEP, good adherence; (2) on PrEP, poor adherence; (3) off PrEP, recent PrEP discontinuation (in last 30 days); and (4) off PrEP, no recent PrEP exposure. Individuals are considered at risk for HIV until the first positive HIV test result or until the last HIV negative test result in the case of administrative censoring, loss-to-follow-up, or another censoring event.

The primary outcome analysis will compare HIV incidence during person-time on PrEP (categories 1 or 2) to HIV incidence during person-time not on PrEP (categories 3 or 4), with a simplified analysis following the analytic methods used by other PrEP open-label studies, and a more complex analysis using marginal structural models to account for time-varying confounding. Secondary outcome analyses will explore whether HIV incidence differs between participants on PrEP with good versus poor adherence (category 1 vs category 2) and whether HIV incidence differs between participants not on PrEP who have recently discontinued PrEP use versus who do not have recent PrEP exposure (category 3 vs category 4).

A more complex primary outcome analysis will be conducted using marginal structural models, following the methods proposed by Robins et al [39] As participants self-select into the PrEP group, the difference in incidence between those on PrEP and not on PrEP may be biased due to confounding. Propensity score methods will be used for bias reduction for the estimation of the causal effect of being on PrEP on HIV incidence, an approach that is well documented in nonrandomized pharmacoepidemiologic studies [40]. This will be an as-treated analysis that will account for discontinuation of PrEP, and as PrEP initiation and cessation may occur over the course of follow-up, and participants may cease and restart sex work, potential confounders may be time-varying, further complicating the estimation of causal effects.

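### The protocol does not say how non-study PrEP is classified, and its weekly and biological measures cannot detect it in off-PrEP time, so the comparator may contain protected weeks

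*Protocol article*

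**What the plan says.** **Outside supply.** Setting and Context states that "The government provides free PrEP to key populations through community-based programs" and that community clinics have been set up to provide it, "including clinics operated by the Rainbow Sky Association of Thailand (RSAT) and Service Workers In Group (SWING) Foundation". The same section says: "All recruitment and study implementation activities are done through SCC, SWING, and RSAT sites in Bangkok and SWING in Pattaya". Two outside suppliers are therefore also study partners. The study product is chemically the same as the local one: "The PrEP drug for the COPE study is Truvada, which contains identical chemical components as Teno-EM" (Daily Oral Pre-Exposure Prophylaxis).

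**Classification.** Data Analysis puts each person-week into one of four categories. The two that make up the comparator are "3) off PrEP, recent PrEP discontinuation (in last 30 days); and (4) off PrEP, no recent PrEP exposure". The primary contrast is categories 1 and 2 against categories 3 and 4. The source of PrEP is not mentioned.

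**Weekly measures.** The SMS survey goes to everyone, but its dose items are limited: "For participants currently using PrEP, additional measures are used to collect information on when they last took PrEP and the number of doses". The stopping rule in Study Visits uses those SMS doses or the pills left over at a medication pickup. Tablet counts are made at the monthly study pickups.

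**Biological measures.** Non-PrEP participants give dried blood spots (DBS) at quarterly visits. Biologic Measures plans a tenofovir diphosphate assay only for participants prescribed PrEP who seroconvert.

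**Survey.** All participants complete the survey at baseline and each follow-up visit. Table 2 gives it a PEP/PrEP domain covering history of use and source, described as focusing on initial knowledge, awareness and attitudes. On health care use, Table 2 says: "Information in this domain is also collected at the final visit to assess any supplemental services that have been accessed outside the study".

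**The concern.** The contrast is only as good as the label on each person-week. A participant who declines study PrEP, or stops it, and takes free PrEP from the national programme would, on the measures described, receive no weekly dose item, have no tablets counted and have no drug level assayed. Unless the survey or a report to staff reveals it, nothing described keeps those weeks out of category 3 or 4.

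Protected weeks in the comparator lower the off-PrEP incidence and pull the hazard ratio toward 1. The same error reaches the economic results, because the Cost-Effectiveness Analysis section takes infections averted from the primary analysis. The inverse probability weights deal with measured confounding and with censoring. They take the recorded treatment as true, so they cannot repair a wrong exposure label.

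**Working it through.** **Inputs from the article.** Sample Size Calculation: off-PrEP incidence 8.5 per 100 PY, 50% reduction, 2% attrition per month, power 0.80, one-sided alpha 0.025, standard-error inflation 0% to 20%, and 1240 in total. Abstract: goal of 620 PY on and 620 PY off PrEP.

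**Step 1: the plan's own figure.** Freedman events = (1.96 + 0.84)² × ((1 + 0.5)/(1 − 0.5))² = 7.85 × 9, or 71 events. The mean rate is (0.085 + 0.0425)/2 = 0.06375, so 71/0.06375 = 1114 PY. Mean follow-up over 12 months at 2% monthly attrition is (1 − 0.98¹²)/(12 × 0.02) = 0.897 years. 1114/0.897 = 1242 participants, which agrees with 1240. This match uses no standard-error inflation.

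**Step 2: effect of outside PrEP in the comparator.** Let c be the share of off-PrEP time covered by outside PrEP. *Assumptions, not in the documents:* the value of c; outside PrEP gives the same 50% reduction; its users have the same underlying risk as other off-PrEP participants.

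- Off-PrEP rate = 0.085 × (1 − 0.5c)
- Observed ratio = 0.0425/[0.085 × (1 − 0.5c)] = 0.5/(1 − 0.5c)
- Events on PrEP = 620 × 0.0425 = 26.35; events off PrEP = 52.7 × (1 − 0.5c)
- SE = √(1/events on + 1/events off)
- Power = Φ(|ln ratio|/SE − 1.96)

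For c = 0: SE = √(1/26.35 + 1/52.7) = 0.239, and 0.693/0.239 − 1.96 = 0.945, giving power 0.83.

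| c | Off rate per 100 PY | Observed ratio | Power, no SE inflation | Power, 20% SE inflation |
|---|---|---|---|---|
| 0% | 8.50 | 0.50 | 83% | 68% |
| 10% | 8.08 | 0.53 | 76% | 60% |
| 20% | 7.65 | 0.56 | 68% | 52% |
| 30% | 7.23 | 0.59 | 58% | 44% |

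If 1240 is read as participants, each state yields 620 × 0.897 = 556 PY. Power without inflation is then 79%, 71%, 63% and 54% (53.5%) down the same rows.

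**Step 3: infections averted.** Per 620 PY on PrEP, the estimate is 620 × (off rate − 0.0425) = 26.35 × (1 − c). That is 26.4 at c = 0, and 23.7, 21.1 and 18.4 at 10%, 20% and 30%. Under these assumptions, infections averted are understated by the fraction c.

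**Step 4: can the described data reveal c?** The primary analysis uses one record per person-week. The weekly dose item covers current users, the pill count covers study pickups, and the assay covers seroconverters prescribed PrEP. The outside-services question is described for the final visit. Only the PEP/PrEP survey domain asks about use and source, and no dated use is described for it. As described, it can show that some outside use occurred but cannot place it in particular weeks.

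**The case against.** Several points on the other side stand.

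- **The definition.** A reader might infer that off-PrEP time means time off study Truvada. The article does not say so. Data Analysis speaks only of PrEP, and the SMS section of current use, with no source named. What can be said is that the rule is unstated and that the weekly measures described would not support an any-source rule.
- **The survey.** A reader might infer that off-PrEP participants are never asked about PrEP. That is wrong: the survey goes to everyone and covers use history and source. Only the weekly dose item is confined to current users. The questionnaire is not reproduced, and the emphasis on initial knowledge leaves the repeat schedule unclear.
- **Cessation.** A reader might infer that changing supplier is recorded as stopping and so spoils the cessation endpoint. Study Visits says that reasons for discontinuing are recorded and that changes in use can be reported at visits, by SMS or to staff at other times. A move to another supplier can therefore be captured.
- **Incentives.** Study PrEP is free and paid for: up to 14,360 THB a year for those who initiate, against 8360 THB for those who do not, and 330 of 445 participants started at baseline. This argues against large-scale use of outside PrEP, but does not exclude it among those who decline or stop study PrEP.
- **Condensed article.** Detailed coding rules may sit in the full protocol or analysis plan. That answers a complaint about missing detail. It does not answer the point that the article fixes who receives the dose item and whose blood is assayed, and that these choices leave outside use undetected week by week.

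**Conclusion.** The point holds in a conditional form. Outside PrEP is a documented alternative at clinics run by the study's own partners. The weekly and biological measures described cannot detect it in the comparator, and the article gives no rule for classifying it. Given equal effectiveness and similar underlying risk, any such use biases the primary ratio and the results built on it toward no effect.

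The size cannot be taken from the documents. The range above (ratio 0.53 to 0.59 and power 76% to 58% at 10% to 30% coverage, 620 PY per state, no inflation) shows sensitivity and does not estimate what happened. Off-PrEP time is already the scarce side: 33 of about 168 PY by February 2019, a shortage that the Discussion anticipates.

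The change is worth making because it is cheap and acts on a measurement rule that the article states.

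**What to change.** 1. In Data Analysis, state that categories 1 to 4 count PrEP from any source.
2. Send the weekly items on last dose and doses in the last 7 days to every participant, with a source option (study or other).
3. At each quarterly computer-assisted interview, ask for dated non-study PrEP and PEP use through the existing use-and-source domain.
4. For time already accrued, run a sensitivity analysis that reclassifies or censors off-PrEP weeks with reported outside PrEP. If weeks are censored, include that censoring in the planned censoring weights.
5. Optionally, assay a sample of the stored DBS from off-PrEP time to estimate the share covered.

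The cost of items 1 to 4 is a slightly longer SMS for non-users, one or two survey questions, a sentence in the exposure definition and one further analysis. Some person-time will move out of the off-PrEP state, which is already short. Item 5 adds laboratory cost, which the documents do not allow to be estimated.
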